#### Biobanking/biomarker study

The identification of circulating biomarkers in a population of CCM patients with recorded clinical history and documented therapeutic response will potentially contribute to establish prognostic and response-to-therapy indicators in the peripheral blood of CCM patients. Biomarkers to monitor CCM are urgently needed and are potentially fruitful according to several reports on other cerebrovascular disorders [34]. Indeed, specific circulating miRNAs have been reported in infantile haemangiomas which respond to propranolol [35], in cerebral aneurisms [36], and for cerebral haemorrhagic and ischaemic stroke [37]. Patients will undergo blood sampling for biobanking at randomization, at 1 month, and at 1 and 2 years of follow-up.

#### Microbiome

In a murine model of FCCMs, it has been reported that the microbiome composition influences the progression of brain angiomas [38]. Recent data in 75 patients go along the same line [39] and therefore it is of interest to characterize patients included in Treat_CCM at baseline as well as during disease evolution. Stools will be sampled for microbiome analysis at randomization, at 1 month, and at 1 and 2 years of follow-up.

### Follow-up phase

Follow-up clinical visits will be performed at weeks 2 and 4 for dose adjustment of the study medication plus adverse events and side effect monitoring, and then every 6 months until the study end at month 24. Visits at 12 and 24 months are mandatory for MRI, and blood and faeces sampling for biobanking. Six-month and 18-month visits can be substituted with a telephone interview by a member of clinical study site staff to check for her/his vital status and whether any serious adverse event has occurred (Fig. 2).

**Fig. 2 Fig2:**
[figure not shown]
Study plan and timeline according to the Standard Protocol Items: Recommendations for Interventional Trials (SPIRIT) statement

### Sample size

To the best of the available knowledge, the 2-year risk of CCM-related events (ICH and FND) was estimated at 10.1% in CCM patients receiving recommended standard care [1]. Upon performing a formal sample size calculation, 834 patients should be included in the study to demonstrate a risk reduction of 50% with a power of 80% at a significance level of one-tailed α = 0.05. This estimate is unrealistic both for the over-optimistic treatment effect size and for the number of patients to be included, incompatible with a rare disease.

Therefore, in order to obtain preliminary data, a pilot study is planned, adopting a confidence interval approach, rather than using the more usual power and statistical significance method [40]. The sample size calculation for the pilot trial is driven by the proposed sample size of the main trial. According to the nature of the pilot study design, an 80% one-sided confidence interval is chosen, instead of the 95% two-sided interval usually considered for formal comparative trials. With 60 patients randomized in a 2:1 propranolol:control ratio, in the absence of a reduction of adverse events, a clinically meaningful effect, defined as ≥50% reduction of the 2-year risk of CCM-related events, can be excluded by the defined 80% upper confidence interval. Otherwise, the study will provide a promising signal of activity.

### Modality of data processing

The data and the samples collected for the study will be processed as coded data. The treating physician will identify each patient within the study with a code. This code will not enable direct identification, unless at the clinical centre where this code will be securely stored together with the patient’s name and surname. For biological analyses, researchers will identify samples and the data connected to them only through this code. No association between the results of scientific investigations on the samples and the patient’s identity will be possible.

De-identified biological samples will be stored, under UNI EN ISO 9001: 2015 regulations (for the following: collection, storage, and distribution of biological samples and related data for scientific research), transferred, and processed with modalities that guarantee their quality, integrity, availability, and traceability. All of the measures for the correct storage and handling will be put in place, according to the study protocol.

Only the treating physician, the monitors, and the regulatory authorities will have access to patient’s data at the clinical centre and will be able to associate the code with patient’s name for verification purposes. In particular situations, and only after the authorization of the clinical centre and of the promotor, Istituto di Ricerche Farmacologiche Mario Negri, its delegates may also have access to identifiable data.

### Quality control and trial monitoring

The safety profile of propranolol is reassuring and is documented by millions of patients of all ages, including infants treated mostly, but not only, for cardiovascular disorders over the last 40 years. Despite the expected very low probability of adverse effects related to propranolol, patients shall be controlled in particular for heart rate, blood pressure, and other adverse reactions possibly attributable to propranolol.

Quality control activities will be applied by the Study Secretariat at IRCCS-Mario Negri (IRFMN) to each stage of data handling to ensure data are recorded and reported in compliance with the protocol. All of the electronic case report forms (e-CRFs) will be reviewed for completeness and accuracy at the Study Secretariat by trained staff; errors and omissions will be entered on data query forms returned to the investigator for resolution. The Data Safety and Monitoring Board (DSMB) will monitor the safety data in the project in an ongoing basis. Serious and non-serious adverse events (SAEs and AEs) that coincide with primary and secondary endpoints will be collected on the e-CRFs and evaluated by the DSMB. Investigators shall report to the Study Secretariat (IRFMN) all SAEs suspected to be related to the study medications or any serious adverse drug reaction (SADR) within 24 h of learning of its occurrence.

On-site monitoring visits will be performed at site opening and at regular intervals throughout the study. On average, four on-site monitoring visits are foreseen for each participating site. During the visit, a certified monitor will verify adherence to the protocol: completeness, accuracy, and consistency of the data; and adherence to Good Clinical Practice (GCP) and local regulations on the conduct of clinical research. The investigator should guarantee access to source documents for the monitor. The clinical monitor will check participant medical records and other trial-related records (source documents) to verify the data reported to the sponsor on the e-CRFs and in all required reports. The clinical monitor will communicate deviations from the protocol to the investigators and will ensure that appropriate action designed to prevent recurrence of the detected deviations is taken and documented. Deviations from study protocol will be entered into the Protocol Deviation Log and communicated to the sponsor. All of the monitoring activities will be documented according to GCP rules and reported to the sponsor.

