#### Study committees

In order to assess primary and secondary endpoints of this open trial, a PROBE design will be adopted. The following procedures will be implemented:
Clearly defined objective outcomes: the primary outcome events of the study are based on objective clinical assessment, and the imaging secondary endpoint will be calculated from MRI examinations read in a central laboratory by experienced neuro-radiologists, unaware of patient identification and study treatment.Blinded Endpoint Adjudication Committee: all outcome events will be adjudicated by blinded adjudication experts. Blinding of all event documentation will be performed by trained personnel at the Study Secretariat. The role of the independent Clinical Event Committee will be to oversee the blinded adjudication of all primary events. This Committee will report to the Steering Committee. Records of all adjudication decisions and of Clinical Event Committee minutes will be maintained.Data handling: at the Study Secretariat, identification of treatment allocation on the e-CRF will only occur where necessary in order to minimize access to treatment information during data handling.Steering Committee: the Steering Committee will include one representative for each participating clinical centre, the Principal Investigator (ED, IFOM, sponsor of the trial), one representative of the Patient’s Association, and a representative responsible for the Study Secretariat and has the full responsibility for the planning, conduction, analysis, publication of the study protocol, and results.Clinical Event Committee (CEC): CEC members will be independent and will not have direct contact with patients randomized into this trial. The main roles and responsibilities of the CEC are: to agree on definitions of the clinical endpoints and on standard procedures for assessing these endpoints, and to validate blindly the events recorded and reported by the Investigators as endpoints of the study. A Clinical Event Committee manual will be prepared and approved by the members of the CEC.Data and Safety Monitoring Board (DSMB): the roles and responsibilities of the Data and Safety Monitoring Board (DSMB) will be defined by the same DSMB with special focus on intensive monitoring of the safety aspects in the whole study population. Safety reports will be made available to the DSMB by the study statistician every 6 months. No specific interim analysis is foreseen for efficacy, unless required by the Steering Committee or DSMB because of safety concern.

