#### Statistical analyses

The main analysis will be performed according to an intention-to-treat (ITT) approach. Therefore, all patients randomized in the study will be included in the analysis. As we cannot conduct inferential statistics on the data collected in the pilot study, we will only compare the proportions of adverse events between the groups to assess the safety of propranolol [42]. A per-protocol analysis is foreseen.

Baseline characteristics will be presented by treatment groups, and descriptive statistics will be performed to assess the success of randomization. Kaplan–Meier curves will be constructed to illustrate the occurrence of adverse events in the study over time.

Concerning the analysis of this pilot study, we are only interested in whether the treatment estimate is larger or smaller than zero. Consequently, it is not necessary to formally undertake a hypothesis test of the results. An extension of the trial in the case of encouraging preliminary results is foreseen. Special care will be paid to the biologic consistency of the different endpoints, even if none of them will yield statistically significant differences.

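### The stated e-CRF and 24-hour reporting rules are narrower than the planned between-arm safety comparison, so non-endpoint adverse events lack like-for-like recording in both arms

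*Protocol article*

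**What the plan says.** Protocol article, Quality control and trial monitoring. The section first says that "patients shall be controlled in particular for heart rate, blood pressure, and other adverse reactions possibly attributable to propranolol". It then states what is collected: "SAEs and AEs) that coincide with primary and secondary endpoints will be collected on the e-CRFs and evaluated by the DSMB". Next comes a duty on investigators to report to the Study Secretariat "all SAEs suspected to be related to the study medications or any serious adverse drug reaction (SADR) within 24 h".

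Follow-up phase. Visits take place "at weeks 2 and 4 for dose adjustment of the study medication plus adverse events and side effect monitoring". When the 6- or 18-month visit is replaced by a telephone call, the caller checks vital status and "whether any serious adverse event has occurred".

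Study committees. The DSMB works with "special focus on intensive monitoring of the safety aspects in the whole study population" and receives a safety report every 6 months.

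Statistical analyses. Because inferential statistics are ruled out, "we will only compare the proportions of adverse events between the groups to assess the safety of propranolol".

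Outcomes. The endpoints are ICH and FND (primary), then seizures, MRI measures, disability, quality of life, depression and anxiety. Heart rate, blood pressure and respiratory reactions are not endpoints.

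**The concern.** A between-arm comparison of adverse events needs the same events to be sought and recorded in the same way in both arms. The stated e-CRF rule selects events by overlap with an endpoint, and propranolol's own reactions do not overlap with any. The stated 24-hour rule selects mainly by suspected relation to the study drug, and one arm has no study drug. In an open-label trial the site makes that judgement knowing the allocation.

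What is at stake is the safety statement. The Discussion names two things that the pilot may at best deliver: reassurance on safety and a rationale for a larger trial. If the recorded safety data consist of endpoint events in both arms plus drug-attributed serious events in essentially one arm, the DSMB reports and the final table cannot show whether other events are balanced or in excess.

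**Working it through.** The plan gives no adverse-event rate, so there is no figure to reproduce. The check sets the sections side by side.

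**1. Route by event type, as the text stands**

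| Event | Asked about or looked for | Stated route to e-CRF, DSMB or Secretariat | Comparable between arms? |
|---|---|---|---|
| ICH, FND, seizures and other endpoint-type events | Yes | e-CRF and DSMB, no arm restriction | Yes |
| Non-serious propranolol-type reaction (e.g. bradycardia, hypotension) | Yes: heart rate and blood pressure checks; weeks 2 and 4 | None stated | Not secured |
| Non-endpoint SAE suspected to be related to study medication | Yes | 24-hour report | No: controls receive standard care alone (Design) |
| Non-endpoint serious adverse drug reaction to another medicine | Yes | 24-hour report under its second limb | Possible in both arms |
| Non-endpoint SAE not suspected to be related | Yes: any SAE, in the 6- and 18-month telephone calls | None stated | Not secured |

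**2. Ascertainment against recording.** The Follow-up phase section is wider than the e-CRF rule: it does not restrict enquiry by causality, endpoint overlap or arm. But it covers asking, and the section that governs collection gives the answers no destination. The week 2 and 4 visits are also framed around dose adjustment, which does not arise for controls.

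**3. Blinded adjudication does not cover the gap.** Under Study committees, the Clinical Event Committee validates events that investigators report as study endpoints. Whether a non-endpoint SAE is suspected to be drug-related stays with the unblinded site.

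**4. Two readings of 'adverse events' in Statistical analyses**

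- If the term means adverse events in general, the collection rule does not secure the data for the comparison.
- If it means ICH and FND, the data are secured in both arms, but the analysis described as assessing safety then contains none of the drug's own side effects.

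Either way the sections do not fit together.

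**5. Illustration of size (assumed inputs).** Let r be the true 2-year risk of a non-endpoint SAE, equal in both arms, and q the share of those events in the propranolol arm that sites judge related. True expected events are 40r v 20r. The 24-hour stream receives 40rq v 0, provided no control event is a serious adverse drug reaction.

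| r | True events | Reported, q = 0.5 | Reported, q from 0 to 1 |
|---|---|---|---|
| 10% | 4 v 2 | 2/40 (5%) v 0/20 | 0 to 4 v 0 |
| 20% | 8 v 4 | 4/40 (10%) v 0/20 | 0 to 8 v 0 |
| 30% | 12 v 6 | 6/40 (15%) v 0/20 | 0 to 12 v 0 |

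Equal true risks can thus appear as anything from no events to an excess on propranolol, depending on q. Neither r nor q comes from the documents. The table describes the 24-hour stream alone and shows a mechanism; it is not a forecast.

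**The case against.** The case on the other side has five parts.

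- **No exclusion is written.** The text says that endpoint-coinciding events will be collected. It does not say that other events will not be, and the 24-hour sentence is an expedited-reporting duty, not a limit on collection. This stands against any wording with 'only'. It does not explain why the collection sentence carries the endpoint qualifier, which would have no purpose if all events were recorded.
- **Wider enquiry exists.** The Follow-up phase section and the heart rate and blood pressure sentence show that these events are looked for, with no arm restriction written. This stands, and it moves the gap from ascertainment to recording.
- **Controls can generate reportable events.** The serious adverse drug reaction limb is not tied to study medication, and controls may take anti-epileptic or headache drugs. A reader might infer that the control SAE count is zero by rule; this limb, and the collection of endpoint-type SAEs in both arms, show that it is not.
- **'Adverse events' may mean CCM events.** The Design section uses adverse clinical events for ICH and FND, and the Sample size section speaks of a reduction of adverse events when it means CCM-related events. On that reading a full control comparison exists. The stated purpose of assessing the safety of propranolol points the other way, so the term is ambiguous.
- **The article condenses a longer protocol.** Version 2.5 is not shown and may record everything. That would excuse silence. Here, however, a narrow rule is stated; if the full protocol is wider, the article misdescribes it and still needs correcting.

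**Conclusion.** The concern holds in limited form. The collection and 24-hour rules under Quality control and trial monitoring are narrower than the enquiry under Follow-up phase, the DSMB scope under Study committees and the comparison under Statistical analyses. If sites follow the collection section as written, endpoint-type events are comparable between the 40 and 20 patients. Non-serious propranolol-type reactions and unrelated non-endpoint SAEs have no assured like-for-like recording, and related SAEs enter through an unblinded judgement that can hardly arise in controls.

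A reader might go further and conclude that the safety comparison has no valid control data, or that safety is the trial's main yield. The documents support neither. Control data exist for all endpoint-type events, SAEs of any kind are asked about in both arms, and the Discussion lists safety reassurance beside the rationale for a later trial.

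The size cannot be derived from the documents. The conclusion rests on reading the endpoint qualifier as restrictive and on the full protocol not saying something wider. The change is worth making because it is cheap and bears on a stated purpose of the pilot; confidence is moderate.

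**What to change.** 1. Reword the collection sentence under Quality control and trial monitoring, for example: 'All AEs and SAEs identified at any contact, irrespective of suspected causality or overlap with an endpoint, are recorded on the e-CRF in both arms and tabulated by arm in the 6-monthly DSMB report. In addition, SAEs suspected to be related to study medication and all SADRs are reported to the Study Secretariat within 24 h.'
2. In Statistical analyses, use separate terms for adverse events (safety) and CCM-related endpoint events (ICH, FND), and say which one the group comparison and the Kaplan–Meier curves refer to. Use the same terms in Design and Sample size.
3. If version 2.5 of the protocol already has the wider rule, correct the article to match.

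The cost is an e-CRF page, revised wording and modest data entry for 60 patients. The limit is timing. By the end of April 2019, 57 of the planned 60 (95%) were enrolled, so the week 2 and 4 contacts had passed for all but the most recent. The first patient entered in March 2018, so no 24-month visit was due before March 2020 and later follow-up could still be captured prospectively. Retrieval of earlier events from site notes, in an open-label trial, may be incomplete or unequal between arms. Events recorded prospectively after the change should therefore be reported separately from those retrieved.

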#### Study committees

In order to assess primary and secondary endpoints of this open trial, a PROBE design will be adopted. The following procedures will be implemented:
Clearly defined objective outcomes: the primary outcome events of the study are based on objective clinical assessment, and the imaging secondary endpoint will be calculated from MRI examinations read in a central laboratory by experienced neuro-radiologists, unaware of patient identification and study treatment.Blinded Endpoint Adjudication Committee: all outcome events will be adjudicated by blinded adjudication experts. Blinding of all event documentation will be performed by trained personnel at the Study Secretariat. The role of the independent Clinical Event Committee will be to oversee the blinded adjudication of all primary events. This Committee will report to the Steering Committee. Records of all adjudication decisions and of Clinical Event Committee minutes will be maintained.Data handling: at the Study Secretariat, identification of treatment allocation on the e-CRF will only occur where necessary in order to minimize access to treatment information during data handling.Steering Committee: the Steering Committee will include one representative for each participating clinical centre, the Principal Investigator (ED, IFOM, sponsor of the trial), one representative of the Patient’s Association, and a representative responsible for the Study Secretariat and has the full responsibility for the planning, conduction, analysis, publication of the study protocol, and results.Clinical Event Committee (CEC): CEC members will be independent and will not have direct contact with patients randomized into this trial. The main roles and responsibilities of the CEC are: to agree on definitions of the clinical endpoints and on standard procedures for assessing these endpoints, and to validate blindly the events recorded and reported by the Investigators as endpoints of the study. A Clinical Event Committee manual will be prepared and approved by the members of the CEC.Data and Safety Monitoring Board (DSMB): the roles and responsibilities of the Data and Safety Monitoring Board (DSMB) will be defined by the same DSMB with special focus on intensive monitoring of the safety aspects in the whole study population. Safety reports will be made available to the DSMB by the study statistician every 6 months. No specific interim analysis is foreseen for efficacy, unless required by the Steering Committee or DSMB because of safety concern.

#### Centralized laboratories

MRI Core Laboratory (Policlinico MI): examinations will be sent as digital recordings to the MRI Core Laboratory, where a central reading will be performed. A users’ manual for MRI will be made available to the participating centres to ensure common standard methods of image acquisition.Biobank (IRFMN): the coordination of the collection, long-term storage of biological samples in a centralized UNI EN ISO 9001: 2015-certified (for the following: collection, storage, and distribution of biological samples and related data for scientific research) biobank, and distribution of de-identified biological samples. In particular, blood samples will be collected from patients at the time of MRI (randomization, 12 months, and 24 months) and at the 4-week visit.Circulating biomarker assays laboratory (IFOM): serum/plasma samples from patients before the beginning of the treatment will be used to characterize the circulating miRNAs and identify a CCM patient-specific miRNA signature in comparison to age-matched and sex-matched healthy individuals. In addition, we will test the power of the miRNA signature to monitor the response to the pharmacological treatment with propranolol and the progression of the disease [35, 41].Microbioma will be assessed by the 16S technique in stool samples collected at randomization, 12 months, and 24 months [38].

